#### Patient-reported outcomes

HRQoL is assessed with the cancer-specific European Organisation for Research and Treatment of Cancer (EORTC) QLQ-C30 (version 3) questionnaire [64]. The QLQ-C30 is composed of both multi-item scales and single-item measures. These include five functional scales, three symptom scales, a global health status/QoL scale, and six single items, with 30 items in total. All scales and single-item measures range in score from 0 to 100. A high score on the functional scale represents a high level of functioning, a high score for the global health status represents a high HRQoL, but a high score on a symptom scale represents a high level of symptomatology [65].Self-efficacy in coping with cancer is assessed with the 12-item Cancer Behaviour Inventory (CBI-12) (version 2.0) [66, 67]. The questionnaire is scored on a one-dimensional scale, summing up the ratings for the items. A higher score indicates higher levels of cancer-related self-efficacy, with a maximum score of 108.Sleep quality is assessed with the Pittsburgh Sleep Quality Index (PSQI) [68], which has been validated in cancer populations [69]. The questionnaire consists of 19 items grouped into seven component scores. The directionality and interpretation of scores vary across items. A total score ranging from 0 to 21 can be calculated, with a higher score indicating poorer sleep quality. A score < 5 indicates good sleep quality.Insomnia is assessed with the Insomnia Severity Index (ISI) [70], which has also been validated in cancer patients [71]. It contains 7 items and is scored on a one-dimensional scale with a maximum score of 28. The total score is grouped into four categories: no insomnia (0–7), subclinical insomnia (8–14), clinical insomnia (15–21), and severe clinical insomnia (22–28).Sleep patterns, including sleep onset latency (SOL), wake after sleep onset (WASO), early morning awakenings (EMA), time in bed (TiB), total sleep (TST), and sleep efficiency (TST/TiB*100) are measured using the Consensus Sleep Diary [72] 5 days in a row at the three time-points (T1, T2, and T3).

### Adverse events

Adverse events related to the study procedures will be continuously collected throughout the study. In the case of a serious adverse event, this will be reported within a day to study sponsor. Assessment, grading, and reporting of adverse events will follow the detailed guideline from the Exercise Harms Reporting Method (ExHaRM) [73], developed specifically for exercise interventions in oncology populations.

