### Randomization

Recruited participants undergo non-stratified, simple randomization in a 2:1 ratio to either intervention or usual care. The randomization sequence is computer-generated independently through an algorithm used by the Clinical Trial Unit at Aarhus University. When the participants have been randomized, their allocation will be locked in the Research Electronic Data Capture (REDCap) software [42, 43]. The randomization process is not blinded for researchers or participants, as it is not compatible with the study design. Randomization allocation is delivered orally to participants.

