### Sample size

As this study is a feasibility trial, no formal sample size calculation was performed, which aligns with published recommendations [40, 41, 44]. The chosen sample size of 21 participants was based on practical considerations, including recruitment potential, funding constraints, and the high level of participant engagement required for an exercise intervention in this patient population. This decision was also informed by previous feasibility studies investigating exercise interventions in cancer populations with similar feasibility outcomes [45–48]. Recommendations for pilot trials typically suggest a sample size of 10 to 40 participants per group [49–51]. Our 2:1 randomization design (14 interventions, 7 controls) does not fully align with these recommendations due to practical constraints and the need to prioritize intervention feasibility while still maintaining a control group for study design experience and exploratory comparisons. However, the total sample size of 21 participants is consistent with feasibility study guidelines, which emphasize that smaller sample sizes are appropriate when assessing process-related outcomes rather than effect sizes [44].

In the interest of transparency, we acknowledge the precision limitations of our feasibility estimates. Assuming an 80% retention rate with *N* = 21, the 95% confidence interval ranges from 62 to 98%. This wide interval is an inherent limitation of feasibility studies but does not invalidate the study’s objectives. While retention rates in pilot trials are often used to inform sample size calculations for definitive trials, this is not the objective of our study. Instead, our focus is on determining whether trial procedures are practical and achievable within study context.

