### Intervention

The intervention consists of a 12-week exercise program that features three weekly, 2-h training sessions at the Steno Diabetes Centre, Aarhus, facilitated by a physiotherapist experienced in working with cancer patients. The training sessions consist of a joint warm-up session and functional stability exercises (30 min), followed by individual cardiovascular and resistance training (1 h), ending with a joint stretching session (15 min). The cardiovascular training consists of short but high-intensity sessions, aiming for a Borg Rating of Perceived Exertion of 14–20 [52]. The duration of cardiovascular training is increased each week, combined with an increased number of high-intensity intervals, adjusted individually. Progressive resistance training is conducted as circuit training of three sets incorporating both weight machines and floor exercises. The load is gradually increased over time with decreasing repetitions: weeks 1–4 doing 12 repetitions, weeks 5–8 doing 10 repetitions, and weeks 9–12 doing 8 repetitions. The last 15 min of each training session are spent on socializing and evaluating the training. Participants will only be discontinued from the study in the case of the training being assessed as unsafe by study personnel with medical background.

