### Control group

Participants assigned to the control group receive usual care at the Department of Oncology. They will undergo all study measurements at the defined timepoints, similar to the intervention group. For ethical reasons, the participants are informed of the possibility of being referred to training and rehabilitation at municipal service providers through the Department of Oncology. The participants will receive advice regarding training from the physiotherapist during baseline assessments.

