Second, owing to the study design and intervention, blinding of participants and study personnel is not possible during study enrollment and participation. This could make the study susceptible to performance bias. However, we have employed multiple objective outcome measures, which reduce the influence of performance bias. To minimize performance bias in study personnel, the same procedure and guidelines when performing measurements are followed each time despite group allocation of the participants. Selection bias is likewise a concern, as we expect patients to be less likely to participate if they live further away from the hospital, have a full-time job, have limited transportation possibilities, or are older. Therefore, the included participants may not be representative of all endocrine-treated patients with MBC and overweight.

Finally, most exercise intervention studies are at risk of contamination in the control group, as participants randomized to the control group may increase their amount of exercise. This is a concern of the current study. It is suggested that in studies where the control group is offered an intervention rather than usual care only during or after an intervention period, the contamination rate is greatly reduced e.g. by providing accelerometers in the control arm [83]. In this feasibility study, the control group is not offered any intervention; however, we will test the use of accelerometers to possibly implement in a full-scale study in both study arms and thereby decrease the risk of contamination.

In conclusion, this study is an important first step to gain novel insights into the feasibility of exercise in endocrine-treated patients with MBC and overweight. The results from this protocol will decide and guide a future definitive randomized controlled study.

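### Adverse event collection, at least for non-serious events, is limited to those related to study procedures, in an unblinded trial whose arms undergo different procedures

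*Protocol article*

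**What the plan says.** The Adverse events section has three sentences that matter here.

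- Scope of collection: "Adverse events related to the study procedures will be continuously collected throughout the study".
- Serious events: "In the case of a serious adverse event, this will be reported within a day to study sponsor". This sentence states no relatedness condition.
- Standard: "Assessment, grading, and reporting of adverse events will follow the detailed guideline from the Exercise Harms Reporting Method (ExHaRM"), cited as a guideline for exercise trials in oncology. Its content is not reproduced.

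On blinding, the Randomization section says "The randomization process is not blinded for researchers or participants", and Strengths and limitations says "blinding of participants and study personnel is not possible during study enrollment and participation".

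On exposure, the Intervention section says "The intervention consists of a 12-week exercise program that features three weekly, 2-h training sessions". Of controls, the Control group section says "They will undergo all study measurements at the defined timepoints, similar to the intervention group". The planned arm sizes are 14 and 7 (Sample size). Harms appear neither among the feasibility outcomes nor in the progression criteria of Table 1, and no formal tests are planned (Statistical analysis plan).

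**The concern.** The usual order is to record every event and then judge whether it is related. Here the stated scope puts the judgement first, so an event that nobody links to a study procedure has no stated route into the record unless it is serious.

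That matters in this population because attribution is difficult. The Background lists fatigue and physical deconditioning among the effects of the cancer and its treatment, and it cites an earlier trial in which 9 of 33 exercisers stopped because of disease progression, lack of motivation or pain. New pain or tiredness in a patient who trains three times a week can be put down to either cause. A randomised control arm shows the background rate of such events, but only if events are recorded in the same way in both arms.

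At stake is the harm information that goes forward. The Discussion says that exercise has not yet been studied in this population and that the steering committee will assess whether to proceed to a full-scale study. A filtered record could show an excess in the exercise arm that is only background illness, or could hide a real one.

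**Working it through.** The protocol states no adverse event figure, so there is nothing to reproduce. The check is mainly one of reading, followed by an illustration.

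**Step 1: what is collected.** The scope sentence names events related to study procedures. No other section of the article adds all-cause collection.

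**Step 2: who is exposed to what.**

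| Study procedure | Intervention | Control |
|---|---|---|
| Assessments, including the Watt-max cycle test, sit-to-stand, grip strength and blood samples | yes | yes |
| 12 weeks of training, three 2-hour sessions a week | yes | no |

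Training gives 12 × 3 = 36 planned sessions, or 36 × 2 = 72 hours, in one arm only. The same symptom therefore has many more occasions to be called procedure-related in that arm.

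**Step 3: whether the judgement is protected.** Researchers and participants know the allocation, and no blinded assessor is described. The safeguards in Strengths and limitations are objective outcome measures and uniform measurement procedures. Neither governs the decision to record an event.

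**Step 4: illustration.** Let *n* be the planned arm size (14 and 7, Sample size), *r* the true risk of a non-serious event and *a* the share of those events judged related. Then

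expected patients with an event = *n* × *r*; expected number recorded = *n* × *r* × *a*; recorded risk = *r* × *a*.

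Both *r* and *a* are assumptions; the protocol gives neither. With *r* equal in the two arms:

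| *r* | *a*, exercise / control | True expected | Recorded expected | Recorded risk |
|---|---|---|---|---|
| 30% | 30% / 10% | 4.2 / 2.1 | 1.26 / 0.21 | 9% / 3% |
| 30% | 80% / 5% | 4.2 / 2.1 | 3.36 / 0.11 | 24% / 1.5% |
| 50% | 30% / 10% | 7.0 / 3.5 | 2.10 / 0.35 | 15% / 5% |
| 50% | 80% / 5% | 7.0 / 3.5 | 5.60 / 0.18 | 40% / 2.5% |

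First row as an example: 14 × 0.30 × 0.30 = 1.26 and 7 × 0.30 × 0.10 = 0.21. In that row 70% of events in the exercise arm and 90% in the control arm go unrecorded, and equal risks look threefold different.

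The distortion can also run the other way. With an assumed true risk of 50% versus 30% and only 10% judged related in each arm, the recorded risks are 0.50 × 0.10 = 5% and 0.30 × 0.10 = 3%. A difference of 20 percentage points is recorded as 2.

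**The case against.** **Serious events.** A reader might infer that every harm attributed to the cancer goes unrecorded. The text does not support that. The serious-event sentence carries no relatedness condition, so on its plain wording a serious fracture or fall is reported in either arm whatever its cause. Whether the sentence inherits the limit from the one before it is unclear. The firm point is therefore confined to non-serious events.

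**Controls.** It is also tempting to say that the control count is zero by construction. It is not. The limit refers to study procedures, and controls undergo all measurements, including a maximal cycle test. Events related to those can occur and be compared. What is lost is a fair description of overall event rates.

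**Who judges.** The article does not say who decides on relatedness, or when. That the judgement is made with the allocation known is an inference from the two blinding statements. It is a reasonable one, since no blinded assessor is mentioned, but it is not stated.

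**The cited guideline and the full protocol.** The guideline might call for broader collection, and an article commonly leaves event forms to the full protocol. But the reference covers assessment, grading and reporting, not collection, and its content cannot be checked here. If it does require broader collection, the scope sentence conflicts with it and still needs correcting. The objection here is to a scope that is stated, not to missing detail.

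**Other symptom data.** The QLQ-C30 records symptoms in both arms regardless of cause. This helps, but it does not replace event recording.

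**Small numbers.** Safety is not a stated aim, and arm-level rates would be imprecise even with complete recording: an assumed 2 of 7 controls has an exact 95% interval of about 4% to 71%. This stands and limits the gain to description. Imprecision, however, comes from sample size under any collection rule. It neither supports nor excuses the filter.

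**Conclusion.** The concern holds in a limited form. As written, non-serious adverse events are collected only if related to study procedures, in a trial where personnel know the allocation and one arm alone has the training. Such events put down to the cancer or its treatment need not be recorded, and overall rates cannot be fairly described by arm. For serious events the text is ambiguous rather than wrong.

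No size can be taken from the protocol. The figures of 9% versus 3% to 40% versus 2.5% for equal true risks show how the rule can distort; they are not estimates, and they depend on the assumed risks and attribution shares. The conclusion itself depends only on the scope sentence, the blinding statements, the difference in exposure, and the absence from the article of any all-cause provision. It would weaken if the full protocol or the cited guideline provides for all-cause collection, in which case the article's sentence should be made to agree.

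**What to change.** 1. Reword the scope sentence of the Adverse events section so that all adverse events, whatever their cause, are collected in both arms with the same prompt at the existing visits, and severity and relatedness are graded afterwards.
2. State that serious events are reported to the sponsor regardless of relatedness.
3. Tabulate all events and related events by arm, descriptively, and give the steering committee that table with Table 1. This fits the plan to run no formal tests.
4. The Trial status section reports 19 of 21 participants included, so full all-cause recording from baseline is no longer possible for most of them. Apply the change to the remaining visits, report the earlier restricted collection as a limitation, and use all-cause collection in the definitive trial.

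The cost is some extra recording of background disease events in at most 21 patients at visits already scheduled, and a protocol amendment if the sponsor judges that the change needs one under the section on modification of the protocol.

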#### Actigraphy

Daily physical activity and circadian activity rhythms are evaluated with objective measures of rest/wake activity cycles recorded with the ActTrust AT0503 Wrist Actimeter. As we currently have access to only two actigraphs, a randomly selected subset of patients in the intervention arm are asked to continuously wear the actigraph on their non-dominant wrist for a duration of 12 weeks to gain experience using actigraphy tools for data collection in this study design.

### Progression criteria

To ensure that the feasibility objectives in this study are met, progression criteria for each objective are developed [74]. Defining progression criteria is necessary in the interpretation of trial findings. For this purpose, a traffic light system is employed. In this system, a lower (red) threshold indicates major problems that require urgent attention (and perhaps are unfixable), amber indicates minor problems that require attention, and green indicates areas of no concern [74]. As estimates of rates in the feasibility measures are subject to uncertainty, this system allows for chance variation in contrast to definitive thresholds. We will identify fundamental feasibility measures to accurately weigh the importance of each outcome in the assessment. In Table 1, the progression criteria for each outcome are outlined. These criteria are based on relevant studies, as referenced in the background section, and informed by prior research on feasibility outcomes in exercise interventions for breast cancer populations. To provide an overall assessment of the feasibility of the study, we employ a holistic approach, using quantitative measurements of the progression criteria, data from the evaluation questionnaire, and data on feasibility from the qualitative interviews collectively.

**Table 1 Tab1:** Progression criteria for feasibility objectives

Feasibility objective	Red Major problem	Amber Minor problem	Green No concern	Fundamental objective
Recruitment rate	< 25%	25–33%	≥ 33%	Yes
Attendance rate	< 70%	70–80%	≥ 80%	Yes
Retention rate	< 65%	65–80%	≥ 80%	Yes
Acceptability of intervention^a^	< 75%	75–90%	≥ 90%	Yes
Adherence to other study procedures	< 80%	80–90%	≥ 90%	No

Lower and upper threshold values in the traffic light system for feasibility outcomes

^a^Percentage of participants in the intervention group that answers “Yes” to the question: “Would you recommend others to participate in the physical activity program?” in the evaluation questionnaire

#### Participant evaluation surveys

Two questionnaires are used to assess study satisfaction—one for the intervention group and one for the control group. The questionnaire for the intervention group consists of 28 items and investigates different feasibility dimensions: (1) acceptability in terms of satisfaction with the training itself, the exercise equipment, group training, and the intervention overall, and (2) feasibility of the study design, including the amount and length of training sessions, the length of the exercise program and the feasibility of other study procedures. The evaluation questionnaire in the control group is shorter, with only seven items, and investigates acceptability in terms of being randomized to the control group and the load of study procedures.

#### Qualitative evaluation

All participants in the intervention arm are invited to participate in semi-structured qualitative interviews with a clinical nurse specialist [name]. An interview guide is constructed for this purpose, drawing inspiration from relevant studies in the construction hereof [75–77]. Four main areas are investigated: (1) motivation, facilitation, and exercise preferences; (2) barriers to exercise, (3) participation in the intervention, and 4) exercise in the future. These four main areas each investigate multiple aspects of exercise interventions, both generally and in our study. Specific questions in the interview guide are aimed at evaluating feasibility, particularly acceptability. In Table 2, examples of questions from the interview guide that explores feasibility are presented alongside the related evaluation criteria.

**Table 2 Tab2:** Interview questions concerning feasibility outcomes and the respective evaluation criteria

Question	Feasibility dimension	Evaluation criteria
**Did the intervention motivate you?**	Acceptability	If the majority of the participants gained motivation from the intervention
**Have you experience**d** personal challenges by participating in the intervention?**	Acceptability	None or few preventable personal challenges due to participation
**Did the study meet your expectations?**	Acceptability	If the study met or exceeded the expectations in majority of the participants
**Is there anything we could do differently?**	Overall feasibility	No suggestion of major changes
**What could you imagine would be beneficial for us to do to include women in your situation in our study?**	Study design	No suggestion of major changes

### Statistical analysis plan

Data are entered into a REDCap database in real time using electronic case report forms.

Baseline data on participant demographics and characteristics will be presented in a descriptive table in accordance with the CONSORT guidelines [43]. For feasibility outcomes, the analysis will be mainly descriptive and focus on confidence interval estimation and not formal hypothesis testing, in accordance with the CONSORT extension to randomized feasibility and pilot trials [40].

The results of the effect measurements will be presented as means, standard deviations, and effect sizes (standardized mean differences) to assess potential effects, but no formal statistical tests will be performed. Effects will be analyzed at T3 (post-intervention), and further analysis will be made to see if these effects sustain until T4 (12-week follow-up post intervention). The semi-constructed interviews will be digitally recorded, transcribed, and analyzed using thematic analysis [78]. Statistical analyses will be carried out using the Stata 18 software [79].

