### Study design

The FEMA study (Feasibility of Exercise in patients with Metastatic Breast Cancer and Adiposity) is a parallel-group, randomized controlled, feasibility trial with two arms. After providing informed consent, eligible participants are randomly assigned in a 2:1 ratio to the interventional arm, consisting of usual care plus a 12-week exercise program or a usual care-only control arm. Outcome measures are collected at study inclusion (baseline), mid-intervention (6 weeks), post-intervention (12 weeks), and at a 12-week follow-up after the intervention concludes (24 weeks) The study design and timeline are illustrated in Fig. 2 further below.

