#### Body composition

Bioelectrical impedance analysis is measured with the TANITA MC-780MA-N multifrequency segmental body composition monitor to assess changes in weight, BMI, fat mass, muscle mass, visceral fat, basal metabolic rate, and total body water [56].Waist and hip circumference are measured according to the World Health Organization (WHO) [57], measuring waist circumference at the midpoint between the lower margin of the last palpable rib and the iliac crest and hip circumference around the widest portion of the buttocks. A waist-hip ratio is calculated.

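### Effect outcomes are to be summarized by means, SDs and standardized mean differences, with no interval listed and no stated role for baseline, at about 14 versus 7 patients

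*Protocol article*

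**What the plan says.** The Statistical analysis plan section of the protocol article treats the two sets of outcomes differently.

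- **Feasibility outcomes:** "For feasibility outcomes, the analysis will be mainly descriptive and focus on confidence interval estimation and not formal hypothesis testing".
- **Effect outcomes:** "The results of the effect measurements will be presented as means, standard deviations, and effect sizes (standardized mean differences) to assess potential effects". The same sentence then rules out testing: "but no formal statistical tests will be performed".
- **Timing of the effect analysis:** "Effects will be analyzed at T3 (post-intervention), and further analysis will be made to see if these effects sustain until T4".

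The effect paragraph mentions neither an interval nor the T1 value. Baseline appears in that section only for the descriptive table of participants. The T1 values do exist: the Study design section says "Outcome measures are collected at study inclusion (baseline), mid-intervention (6 weeks), post-intervention (12 weeks", and goes on to add the 24-week follow-up.

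Allocation is by "non-stratified, simple randomization in a 2:1 ratio". The Sample size section gives the expected split: "Our 2:1 randomization design (14 interventions, 7 controls".

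**The concern.** The second aim is to look for potential effects, and the plan then asks whether those effects last to T4. With about 21 patients, a table of SMDs will contain sizeable values in both directions by chance. If each SMD stands without an interval, the reader has no direct way to judge whether there is an effect whose persistence is worth discussing.

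The T1 measurements could reduce the noise at almost no cost, but the text does not say whether or how they enter. Raw T3 values, change from T1 and T1-adjusted differences can give visibly different answers in a sample this small. Allocation is open to the researchers, so the choice is better fixed before the arms are compared.

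**Working it through.** **The plan's own precision figure.** The only one is for retention: 80% with N = 21, 95% interval 62 to 98%. It reproduces with a t quantile on 20 df: 0.80 ± 2.086 × √(0.8 × 0.2 / 21) = 0.80 ± 0.182, or 61.8 to 98.2%. No such figure is given for the effect outcomes.

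**Inputs.** Arm sizes 14 and 7 (Sample size) and simple randomization (Randomization). The documents give no correlation r between T1 and T3, so r = 0.5 to 0.8 is assumed. Normal outcomes with equal SDs are also assumed.

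**1. Standard error of an SMD near zero.** √(1/14 + 1/7) = √0.2143 = 0.463 SD.

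**2. Interval around an observed SMD of 0.5.** The t value is 0.5 / 0.463 = 1.080 on 19 df. Inverting the noncentral t gives −0.43 to 1.41. The large-sample formula agrees: 0.5 ± 1.96 × √(0.2143 + 0.5²/(2 × 21)) = 0.5 ± 0.92, or −0.42 to 1.42.

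**3. Chance findings under no effect.** P(|SMD| ≥ 0.5) = P(|t₁₉| ≥ 1.080) = 0.294. As an example, the QLQ-C30 yields 5 + 3 + 1 + 6 = 15 scales and items, so about 15 × 0.294 = 4.4 of them would be expected to reach 0.5 in one direction or the other.

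**4. Chance imbalance at T1.** The SD of the baseline difference is also 0.463, so P(imbalance > 0.5 SD) = P(|z| > 1.080) = 0.280. An imbalance of 0.5 SD moves a raw T3 difference by r × 0.5, which is 0.25 SD at r = 0.5 and 0.40 SD at r = 0.8. This is part of the sampling error in step 3, not an addition to it.

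**5. Smaller arms.** At 80% retention (about 11 and 6) the SE is √(1/11 + 1/6) = 0.51, and the interval around an SMD of 0.5 is −0.52 to 1.50. Simple randomization gives exactly 14:7 with probability 18%, and five or fewer controls with probability 25%.

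**6. What T1 adjustment would give.** At 14 versus 7, in units of the outcome SD:
- ANCOVA: SE = 0.463 × √(1 − r²) × √(1 + 1/(21 − 4))
- Change from T1: SE = 0.463 × √(2(1 − r))

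| r (assumed) | Raw T3 | Change from T1 | ANCOVA | ANCOVA 95% half-width |
|---|---|---|---|---|
| 0.5 | 0.46 | 0.46 | 0.41 | 0.87 |
| 0.7 | 0.46 | 0.36 | 0.34 | 0.71 |
| 0.8 | 0.46 | 0.29 | 0.29 | 0.60 |

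The half-widths use t quantiles and refer to the mean difference. The unadjusted half-width is 2.093 × 0.463 = 0.97 SD. The gain equals a sample (0.463/0.413)² = 1.26 times as large at r = 0.5 and (0.463/0.340)² = 1.85 times at r = 0.7. Even the adjusted interval is wide, so it needs to be shown either way.

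**The case against.** A reader might infer that the plan has chosen raw, unadjusted T3 contrasts, discards T1 and rules out intervals. The documents do not support that.

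- **Use of T1.** The text does not say what the SMD is computed on. The Body composition section says the impedance measurement is used "to assess changes in weight, BMI, fat mass, muscle mass, visceral fat", which fits change from baseline. A condensed article may also leave the effect model to a fuller plan.
- **Intervals.** The plan excludes tests, not intervals. It also promises SDs, and with the arm sizes these let a reader work out an unadjusted interval.
- **Bias.** Randomization leaves the raw difference unbiased, so adjustment buys precision. The small-sample correction to an SMD is trivial here: 1 − 3/(4 × 19 − 1) = 0.96, which turns 0.50 into 0.48.
- **Consequence.** No progression criterion in Table 1 uses an effect outcome, and the article says openly that the study is small and not powered for hypothesis testing.

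All of this stands and limits the point. It does not remove it. The section states which summaries will be shown, and the interval named for feasibility outcomes is absent from the list for effects. An SMD of change scores would lack an interval just the same. A reader could not rebuild an adjusted interval from arm-level means and SDs alone. Having no tests makes intervals more useful, and the article applies that standard to retention.

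**Conclusion.** The point holds in limited form. The effect summaries named are means, SDs and SMDs at T3 and T4. No interval is listed, and the available T1 values have no stated role. At the expected 14 versus 7, an SMD of 0.5 is compatible with anything from about −0.43 to 1.41, and an SMD that large arises by chance for about 29% of outcomes.

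These figures rest on the expected split, complete data, and roughly normal outcomes with equal SDs. With losses the intervals widen. The benefit of adjustment depends on the assumed correlation: it is modest at 0.5 and substantial at 0.7 or above. The same formula applies at T4 with the T1–T4 correlation, which the documents also do not give.

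Severity is low to moderate. The effect analysis is exploratory and does not drive the decision on a full-scale trial. The change is a nearly free improvement to how aim 2 is reported.

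**What to change.** Add two or three sentences to the analysis text:

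- For each continuous effect outcome, estimate the difference between arms at T3, and at T4 where the outcome is measured then (the sleep diary is scheduled only to T3), by ANCOVA with the T1 value as covariate.
- Report that difference with a 95% confidence interval, in original units where the outcome has them. The metabolic score, a sum of Z-values, stays on its own scale.
- If an SMD is also shown, say which values and which SD it is based on, and give its 95% confidence interval.
- Keep the commitment to run no hypothesis tests, and read persistence at T4 from the estimates and their intervals.

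The cost is one degree of freedom and one simple Stata model per outcome and time point, with no new data. The Trial status section reports 19 of 21 participants included, so the analysis is among the parts that can still be changed. The wording should be fixed before the arms are compared.

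If a fuller plan already specifies the use of T1 and the intervals, the article needs only to say so.
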